#### Secondary outcome measures.

5-year DFS: The proportion of patients who remain free of disease recurrence (local or distant) five years after surgical intervention.3- and 5-year Overall Survival: The proportion of patients alive at 3- and 5-years post-treatment, regardless of disease status.3- and 5-year Local Recurrence Rate: The percentage of patients experiencing tumor recurrence at the primary site (anastomosis or pelvis) within 3 and 5 years.1-, 3- and 5- year Colorectal Cancer Specific Quality of Life: Patient-reported outcomes assessed using the New Cleveland Clinic Colorectal Cancer Quality of Life Questionnaire [14].1-, 3- and 5- year Bowel Dysfunction Related Quality of Life: Patient-reported outcomes assessed using the low-anterior resection syndrome (LARS) score [15].

Fig 1 represents the timeline of anticipated recruitment and outcome measures.

**Fig 1 pone.0321819.g001:**
[figure not shown]
The timeline showing patient recruitment and measurement timeframes for outcome measures.

### Sample size and recruitment

The literature reports a mean 3-year disease-free survival rate of 75–85% for the sample to be included in the study [16]. For patients with mid-rectal tumors (cT2N+ and cT3N0) without high risk MRI findings, the 3-year disease-free survival rate was estimated to be 80% for both direct TME and TME following neoadjuvant chemoradiotherapy. Under these conditions, with α = 0.05 (95% confidence interval) and 80% power, the power analysis indicated that a total of 396 patients (1:1 ratio) would be required. Considering a 10% dropout rate, it is planned to include 218 patients in each group, for a total of 436 patients.

According to data from the Turkish Ministry of Health, General Directorate of Public Health, a total of 24,312 patients were diagnosed with rectal cancer between 2020 and 2024, of whom 17,896 underwent surgery (https://hsgm.saglik.gov.tr/tr/kanser.html). Since this study will be conducted nationally under the sponsorship of the main society of Turkish colorectal surgeons TSCRS, we anticipate reaching the targeted patient number within five years from the start of the study. To achieve this goal, TSCRS will utilize various channels, including mailing, social media, and its website, to announce the study and inform surgeons about the protocol.

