### Statistical methods

During the study, missing data analyses and data quality assessments will be actively conducted, and measures to prevent data loss and enhance data quality will be implemented as appropriate. All statistical analyses will be conducted by experts from the TSCRS Biostatistics and Bioinformatics Analysis Unit using SPSS (SPSS Inc, Chicago, IL) software packages.

Multivariable regression analyses will be conducted to evaluate the effect of treatment strategy (direct TME vs. nCRT followed by TME) on the primary and secondary outcomes. The following covariates will be included in the models based on clinical relevance and literature review: age, sex, clinical T stage (cT2 vs. cT3), clinical N stage (N0 vs. N+), tumor differentiation, regimens of neoadjuvant treatment (long-course CRT, short-course RT, TNT with long or short-course RT), interval between neoadjuvant RT/CT and surgery, comorbidities (e.g., Charlson Comorbidity Index), performance status, postoperative complications (Clavien-Dindo), tumor histology, pathologic TME quality (pathologic completeness of the mesorectum), and center effect (as a random effect if appropriate).

For time-to-event outcomes such as disease-free survival (DFS) and overall survival (OS), Cox proportional hazards regression models will be used to estimate hazard ratios and 95% confidence intervals. The proportional hazards assumption will be tested using Schoenfeld residuals.

To address potential selection bias due to the non-randomized design, propensity score methods will be applied. Specifically, propensity scores for receipt of nCRT (vs. direct TME) will be estimated using logistic regression including the aforementioned covariates. The primary analysis will adjust for the propensity score as a covariate in the Cox model. Sensitivity analyses will be conducted using propensity score matching (1:1 nearest neighbor matching without replacement) and inverse probability of treatment weighting (IPTW) to ensure the robustness of results.

Patients lacking the main data specified in the inclusion and exclusion criteria, demographic data, or follow-up data related to the primary endpoint will be completely excluded from the study. Patients with missing data from other variables or secondary endpoints will only be excluded from those specific analyses, and secondary endpoints will be evaluated using data from patients with complete datasets.

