## Discussion

In line with current recommendations, some surgeons perform upfront TME for patients with T2-3 node-positive mid-rectal cancer in the absence of MRF involvement. However, in these cases, the common approach is to administer neoadjuvant chemoradiotherapy. This study seeks to evaluate whether upfront TME achieves non-inferior 3-year disease-free survival compared to the standard.

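### The sample size of 396 cannot be derived from its stated inputs: no margin or sidedness is given, and α = 0.05 paired with a 95% confidence interval leaves open whether power is 80% or about 70%

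*Protocol article*

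**What the plan says.** All the inputs stand in one paragraph of the Protocol article, under Sample size and recruitment:

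- Outcome rates: "the 3-year disease-free survival rate was estimated to be 80% for both direct TME and TME following neoadjuvant chemoradiotherapy".
- Error rates and result: "with α = 0.05 (95% confidence interval) and 80% power, the power analysis indicated that a total of 396 patients (1:1 ratio") would be required. The article does not say whether α is one-sided or two-sided.
- Inflation: "Considering a 10% dropout rate, it is planned to include 218 patients in each group, for a total of 436 patients".

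The type of comparison has to be gathered from other sections. The Discussion frames it as non-inferiority: "This study seeks to evaluate whether upfront TME achieves non-inferior 3-year disease-free survival compared to the standard". Main question instead sets a null of no difference against an alternative that direct TME is worse, with no margin in either. Statistical methods says that "Cox proportional hazards regression models will be used to estimate hazard ratios and 95% confidence intervals". A 10% difference appears only in the section on adverse events and discontinuation, as a ground for ending the study.

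**The concern.** With the same rate assumed in both groups, the true difference is zero. No sample size gives 80% power to detect a difference of zero, so some margin must have entered the calculation. The paragraph sets out its inputs but omits the one that drives the answer.

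The error rate is also unclear. In a non-inferiority test, one-sided α = 0.05 corresponds to a two-sided 90% interval, or equivalently a one-sided 95% bound. An ordinary two-sided 95% interval corresponds to one-sided 2.5%. Pairing α = 0.05 with a 95% confidence interval can be read either way, and the two readings give different power for the same 396 patients.

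The study is meant to support leaving out nCRT in selected patients. If neither margin nor interval is fixed in advance, the rule for calling direct TME non-inferior could be settled after the results are known, and a reader cannot tell how likely an inconclusive result is.

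**Working it through.** **Inputs from the article.** 3-year DFS 80% in both groups; α = 0.05; power 80%; 1:1 split; 396 evaluable; 10% dropout; 436 enrolled.

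**Inputs that must be supplied.** Margin m and one-sided error rate a.

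**Formula.** For a difference in proportions with equal true rates p, n per group = (z₁₋ₐ + z₀.₈₀)² × 2p(1 − p) / m². Here 2p(1 − p) = 2 × 0.8 × 0.2 = 0.32 and z₀.₈₀ = 0.8416.

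**Step 1: reproduce 396.** Take m = 0.10 and a = 0.05:
(1.645 + 0.8416)² × 0.32 / 0.01 = 197.8, rounded up to 198 per group, 396 in total. The match is exact.

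**Step 2: same margin, two-sided 95% interval (a = 0.025).**
(1.96 + 0.8416)² × 0.32 / 0.01 = 251.2, rounded up to 252 per group, 504 in total.

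**Step 3: power at 198 per group with m = 0.10.** The standard error is √(0.32 / 198) = 0.0402.
- One-sided 5%: Φ(0.10/0.0402 − 1.645) = 80.0%.
- One-sided 2.5%: Φ(0.10/0.0402 − 1.96) = 70.1%. The chance of an inconclusive result under true equality is then 29.9%.

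**Step 4: margin that gives 80% power at 198 per group.**
- One-sided 5%: 0.0402 × (1.645 + 0.8416) = 10.0 points.
- One-sided 2.5%: 0.0402 × (1.96 + 0.8416) = 11.3 points.

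**Step 5: other calculations tried.** Two-sided superiority of 80% against 90% needs 398, and one-sided superiority of 75% against 85% needs 394. Both come close, but neither is exact and both contradict the stated equal rates. Superiority of 80% against 70% needs 588 (two-sided) or 462 (one-sided). Two-sided equivalence with a 10-point margin needs 550 (5% per side) or 674 (2.5% per side).

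**Step 6: dropout.** 396 × 1.10 = 435.6, rounded to 436, so 10% was added to the evaluable number. Allowing for 10% loss from those enrolled gives 396 / 0.90 = 440. As planned, 436 × 0.90 = 392.4 remain, about 196 per group. Power with a 10-point margin is then 79.7% (one-sided 5%) or 69.7% (one-sided 2.5%). The dropout that 436 can absorb is 1 − 396/436 = 9.2%.

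**The case against.** The strongest reply is that nothing is wrong with the number itself. The alternative hypothesis points in one direction, so a one-sided 5% test with a one-sided 95% bound is a coherent reading of the paragraph. On that reading and a 10-point margin, 396 patients give the stated 80%. This stands: a reader might infer that the study is simply underpowered at 70%, and the documents do not support that. The 70% figure needs both a 10-point margin and a two-sided interval, and the article states neither.

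Nor does the article show that the margin was 10 points. A margin of about 11.3 points with a two-sided 95% interval also gives 80% power at 396. The exact match and the round value make 10 points likely, but the 10% elsewhere in the article is a criterion for ending the study, not a margin.

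The 95% intervals in Statistical methods add little. They concern estimated hazard ratios and contain no rule comparing an interval with a margin, so the ambiguity rests on the wording of the sample size paragraph.

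A reader might also infer a definite power loss from unequal groups, because the Discussion says "However, in these cases, the common approach is to administer neoadjuvant chemoradiotherapy". That sentence refers to node-positive tumours, whereas cT3N0 is also eligible. The Interventions section describes both strategies as widely used, and recruitment is to continue until the required number is reached. No expected split is given, so no power figure for imbalance can be derived. What can be said is that 80% power assumes a 1:1 split, which an observational design does not control.

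Finally, the dropout slip is too small to carry the point: 4 patients and about 0.4 percentage points of power.

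Condensation into an article does not answer the core. The article chose to publish its power calculation, and as published the calculation lacks the quantities that determine its result.

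**Conclusion.** The point holds as one of incoherent and incomplete inputs. Equal 80% rates, α = 0.05 and 80% power do not yield 396 without a margin and a sidedness. The best reconstruction is a 10-point margin at one-sided 5%, which is an inference.

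The practical consequence is conditional. With a 10-point margin, 396 evaluable patients and a 1:1 split, power is 80% if the decision uses a two-sided 90% interval or a one-sided 95% bound, and about 70% if it uses a two-sided 95% interval. These figures rest on the assumed 80% rate. Over the 75–85% range that the article quotes, power with the two-sided 95% interval runs from 63% to 80%, and with one-sided 5% from 74% to 87%.

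Separately, and as a minor matter, the enrolment target falls 4 short of what the plan's own 10% dropout requires.

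**What to change.** Restate Main question and Sample size and recruitment together. The null hypothesis should be that direct TME is worse by at least the margin, and the alternative that it is not. State the margin actually used, the one-sided α and the interval that decides the result. Two versions are coherent:

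- (a) One-sided 5%, decided by a two-sided 90% interval or a one-sided 95% bound. If the margin is 10 points, 396 evaluable patients and 80% power stand.
- (b) A two-sided 95% interval, with power at 396 restated as about 70% for a 10-point margin. Restoring 80% at that margin would take 504 evaluable patients, or 504 / 0.90 = 560 enrolled.

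Correct the inflation to 440, or say that 436 allows for 9.2% dropout. Add a sentence that the stated power assumes a 1:1 split, which the design does not control.

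The cost is a rewording of two short sections and at most 4 more patients for the inflation. Under (b) the stated power becomes less favourable. The article says that recruitment had not begun, so the change can be made before any outcome data exist.

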### Data collection and management

Researchers will input patient data into the electronic database which is currently used in the TSCRS prospective registry (Redcap). This database includes all variables regarding demographic, clinical, surgical, oncologic and functional outcomes of the patients (S2 File). The patients’ baseline clinical tumor stages, clinical tumor stages before and after neoadjuvant treatments, type of surgery, early and late postoperative complications, postoperative pathological tumor stages, imaging results from the routine rectal cancer follow-up protocol, recurrence, and survival data will be prospectively entered into the database by the researchers. Patient reported outcomes will be collected by electronic surveys via TSCRS website. The Turkish versions of New Cleveland Clinic Colorectal Cancer Quality of Life Questionnaire [14] and LARS score [15] have been validated before.

Centers that submit support letters by the specified deadline will have a RedCap username and password created for each researcher in the TSCRS prospective database. Each center can participate in the study with a team consisting of one supervisor/faculty member/specialist doctor and a two-person data collection team (a physician, a medical specialty student, or a medical school student), making a total of three people. The team members are responsible for collecting the data, entering it into the database under the conditions set by the steering committee, and communicating with the research secretary when necessary. The supervisor of the team is responsible for the security and accuracy of the data. The entered data will be reviewed and approved by the controller researchers (TB, AEC) and the study secretary (employed by TSCRS) for reliability and errors.

#### Access to data and confidentiality.

All protocols have been shared on open-access platforms including clinicaltrials.gov and the website of the trial (https://arastirma.tkrcd.org.tr/). Access to the database containing patient information will be restricted to the steering committee only. The database may be shared with authorities upon request from ethical committees and health authorities. Upon request, de-identified patient information may be shared with third parties and external researchers.

The data entered into the database by the investigators transferred to the SPSS worksheet by the study secretary and stored in a digital cloud system (Microsoft OneDrive) accessible only to steering committee and the study secretary. Consent forms will be delivered to the study secretary by the center supervisors and stored in the cloud by the study secretary. All physical and digital data collected during the study will be retained for 3 years after the completion of the study (a total of 8 years from the start of the study) and will then be permanently destroyed.

### Statistical methods

During the study, missing data analyses and data quality assessments will be actively conducted, and measures to prevent data loss and enhance data quality will be implemented as appropriate. All statistical analyses will be conducted by experts from the TSCRS Biostatistics and Bioinformatics Analysis Unit using SPSS (SPSS Inc, Chicago, IL) software packages.

Multivariable regression analyses will be conducted to evaluate the effect of treatment strategy (direct TME vs. nCRT followed by TME) on the primary and secondary outcomes. The following covariates will be included in the models based on clinical relevance and literature review: age, sex, clinical T stage (cT2 vs. cT3), clinical N stage (N0 vs. N+), tumor differentiation, regimens of neoadjuvant treatment (long-course CRT, short-course RT, TNT with long or short-course RT), interval between neoadjuvant RT/CT and surgery, comorbidities (e.g., Charlson Comorbidity Index), performance status, postoperative complications (Clavien-Dindo), tumor histology, pathologic TME quality (pathologic completeness of the mesorectum), and center effect (as a random effect if appropriate).

For time-to-event outcomes such as disease-free survival (DFS) and overall survival (OS), Cox proportional hazards regression models will be used to estimate hazard ratios and 95% confidence intervals. The proportional hazards assumption will be tested using Schoenfeld residuals.

To address potential selection bias due to the non-randomized design, propensity score methods will be applied. Specifically, propensity scores for receipt of nCRT (vs. direct TME) will be estimated using logistic regression including the aforementioned covariates. The primary analysis will adjust for the propensity score as a covariate in the Cox model. Sensitivity analyses will be conducted using propensity score matching (1:1 nearest neighbor matching without replacement) and inverse probability of treatment weighting (IPTW) to ensure the robustness of results.

Patients lacking the main data specified in the inclusion and exclusion criteria, demographic data, or follow-up data related to the primary endpoint will be completely excluded from the study. Patients with missing data from other variables or secondary endpoints will only be excluded from those specific analyses, and secondary endpoints will be evaluated using data from patients with complete datasets.

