#### Adverse event reporting, safety and criteria for discontinuing.

In this study, a non-standard treatment that is not currently implemented will not be evaluated. Consequently, side effects and adverse events will be documented as part of the routine monitoring process. However, the steering committee (TB, AEC) will assess interim analyses regarding any safety measures every six months. The study will be terminated if a new treatment relevant to patient groups in rectal cancer management is introduced during the study period and included in the guidelines, and/or there are unacceptable disease-free survival or local recurrence rates (a difference of more than 10%) in any treatment arm that could adversely affect the success of the project. To ensure the safe conduct of the project in the event of such risks, measures will be taken and monitored by the steering committee. The TSCRS will inform relevant parties and all members through e-mail, society website and social media accounts regarding important protocol amendments.

The study will continue until the necessary number of patients is reached. The study will be terminated if a new treatment relevant to patient groups in rectal cancer management is introduced during the study period and included in the guidelines, and/or there are unacceptable disease-free survival or local recurrence rates (a difference of more than 10%) in any treatment arm.

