### Limitations

The non-randomized, observational design introduces the potential for selection bias. Although propensity score methods will be used to minimize selection bias, residual confounding may persist. Our study is expected to span at least five years, which presents logistical challenges both in terms of patient recruitment and follow-up. By the end of this period, the relevance and generalizability of the results may be limited due to potential changes in clinical practice and evolving treatment standards.

Moreover, the trial’s reliance on MRI-based risk stratification may lead to variability in interpretations across different centers, particularly in the absence of centralized imaging review. Another limitation is the absence of central pathology review, which may impact the consistency of histopathological assessments. To minimize these limitations, standard MRI and pathology assessments have been published on the study website. Additionally, standardized MRI and pathology evaluation protocols were presented during a webinar organized for candidate participating centers. Furthermore, the TSCRS commits to providing central review and support in cases where centers require assistance with MDT, MRI, or pathology evaluations.

Unfortunately, MSI testing is not yet performed as a standard procedure in endoscopic pathology in Türkiye. Many centers offer it only as an additional test, which is time-consuming, often not covered by insurance, and results in extra costs for patients. Therefore, MSI is tested in endoscopic pathology only if it is routinely performed at the center or if the patient consents to undergo testing at another institution at an additional cost. For this reason, we could not specify unknown pre-treatment MSI status as an exclusion criterion. However, MSI testing is routinely performed in final surgical pathology in our country. Patients found to have MSI positivity in surgical pathology will not be included in the final analysis. Similarly, patients who underwent preoperative MSI testing (if performed), were found positive, and/or received immunotherapy will also be excluded from the final analysis.

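### The stated covariate list, which also feeds the propensity score, has no calendar-time term, so drift over up to five years of accrual would go unadjusted in every planned analysis

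*Protocol article*

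**What the plan says.** Statistical methods introduces the adjustment set with "The following covariates will be included in the models based on clinical relevance and literature review". The list covers patient, tumour, treatment, complication and pathology variables and ends with "pathologic TME quality (pathologic completeness of the mesorectum), and center effect (as a random effect if appropriate"). It contains no year, date or accrual period.

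The same list is carried forward. The propensity score is to be "estimated using logistic regression including the aforementioned covariates", and "The primary analysis will adjust for the propensity score as a covariate in the Cox model". The sensitivity analyses are "propensity score matching (1:1 nearest neighbor matching without replacement) and inverse probability of treatment weighting (IPTW"); no other propensity model is named. The Restaging section allows between-centre variation in restaging as further regression variables, but says nothing about time.

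On design and timing:

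- Trial design and Interventions describe a non-randomized cohort treated in routine care, with patients sorted into groups when the study ends.
- Trial registration and ethical considerations gives an anticipated recruitment period from August 2025 to August 2030. Sample size and recruitment expects the target to be met within five years.
- Limitations, speaking of the end of that period, says "the relevance and generalizability of the results may be limited due to potential changes in clinical practice and evolving treatment standards". It treats this as a limit on how far the results apply, not as a threat to the comparison between groups.

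**The concern.** In a non-randomized cohort, calendar time is a confounder if it is related both to which treatment is chosen and to outcome. The article makes both links plausible. The Introduction describes the need for nCRT as debated and reports that European and North American guidelines differ, so the treatment mix may shift during accrual. Investigators also receive reports twice a year, and interim results are to be presented at meetings, so the clinicians who choose treatment may see emerging information. Outcome may drift as surgery, imaging or systemic treatment changes.

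The centre effect does not stand in for time, because drift happens within centres. The two sensitivity analyses do not help either: they use the same covariates, so they would agree with the primary analysis whether or not time confounds it. What is at stake is the comparison meant to show whether nCRT can be omitted without loss of 3-year DFS. A time trend would be read as a treatment effect.

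**Working it through.** **1. The plan's own figure.** Sample size and recruitment gives 396 patients in total for 80% DFS in both groups, alpha 0.05 and 80% power. No margin is stated there. An assumed margin of 10 points with one-sided alpha 0.05 returns the figure:

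n per group = (1.645 + 0.842)² × 2 × 0.80 × 0.20 / 0.10² = 197.8, so 198 per group and 396 in total.

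Adding 10% gives 198 × 1.10 = 217.8, so 218 per group and 436 in total, as stated. The point disputes none of these figures. The inferred margin and one-sided alpha are used only in step 4.

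**2. Is calendar time in any model?** Reading the chain in Statistical methods:

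| Analysis | Covariates | Calendar term |
|---|---|---|
| Multivariable models | named list | none |
| Propensity score | same list | none |
| Primary Cox model | that propensity score | none |
| Matching, IPTW | that propensity score | none |

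**3. Size of the bias.** Inputs: accrual of 5 years (the document's upper limit); even overall recruitment (assumed); direct-TME share rising linearly from 20% to 50% (assumed); 3-year DFS drifting linearly by 1 to 2 points per year (assumed).

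Share at time t: s(t) = 0.20 + 0.06t, for t from 0 to 5.

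- Direct TME: ∫s dt = 1.00 + 0.75 = 1.75; ∫t·s dt = 2.50 + 2.50 = 5.00; mean entry = 5.00 / 1.75 = 2.86 years.
- nCRT: ∫(1 − s) dt = 5 − 1.75 = 3.25; ∫t(1 − s) dt = 12.5 − 5.0 = 7.5; mean entry = 7.5 / 3.25 = 2.31 years.
- Gap in mean entry = 2.86 − 2.31 = 0.55 years.
- Bias = gap × drift = 0.55 × 1 to 0.55 × 2, or about 0.5 to 1.1 points.

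If the share is constant the gap is 0, and if DFS does not drift the multiplier is 0. Either way the bias vanishes.

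**4. What that would do to the test.** Take 198 per group, the inferred 10-point margin and one-sided alpha 0.05.

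- Bias favouring direct TME, with true DFS 70% against 80%: SE = √[(0.21 + 0.16)/198] = 0.0432. Type I error = Φ(bias/SE − 1.645), which is 6.5% at 0.55 points and 8.2% at 1.10 points, against a nominal 5%.
- Bias against direct TME, with true DFS 80% in both groups: SE = √(0.32/198) = 0.0402. Power = Φ((0.10 − bias)/SE − 1.645), which is 76% at 0.55 points and 72% at 1.10 points, against 80%.

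These are indicative only. The assumed shares average 1.75/5 = 35% direct TME, so actual groups would not be equal.

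**The case against.** **The list may not be closed, and an analysis plan could add a term.** The text does not say that only these covariates will be used. But it names them, and it ties the propensity score to exactly that set. An adjustment set that is stated and reused in this way can be judged as it stands.

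**The effect is small and rests on assumptions.** This stands. Both drifts are assumed, and 1 to 2 points per year is 5 to 10 points over five years; the upper end spans the whole 75–85% literature range quoted for the sample size. Five years is an upper limit, and faster accrual would shrink the gap. The rule ending the study if a relevant new treatment enters guidelines limits abrupt change, though it does not deal with gradual drift. Limitations speaks of potential change, not expected change.

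**A stronger reading does not hold.** The article plans that "it is planned to include 218 patients in each group, for a total of 436 patients", says that "The study will continue until the necessary number of patients is reached", and calls nCRT the common approach. A reader might infer that the nCRT group closes once it has 218 patients, leaving later direct-TME patients without concurrent comparators. At assumed flows of 2:1 to 3:1 that would affect half to two thirds of them, with a bias of 1.3 to 3.3 points. The document does not support this. Interventions forms the groups only at the end of the study, 218 is the output of a sample-size calculation, and the stopping sentence concerns the study as a whole. Those figures should not be used.

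**The direction is not settled.** A reader might also assume that the bias favours direct TME. If direct TME becomes more common and outcomes improve, it does. But the nCRT group includes total neoadjuvant regimens; if their use grows, nCRT patients could be the later ones and the sign reverses.

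**A usable date may be lacking.** The dates listed under Restaging concern neoadjuvant patients only. Written consent, however, is required from every eligible patient before any treatment, so one common entry date exists for both groups.

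**Conclusion.** The point holds as a modest, avoidable gap in bias control. Calendar time is absent from the stated covariates and hence from the propensity score, the primary Cox model, the matching and the weighting, in a non-randomized study that may recruit for five years. Confounding by time is a risk, not a certainty: it needs a drift in treatment mix together with a drift in outcome. Under the assumptions shown it is about 0.5 to 1.1 points of 3-year DFS, in a direction the document does not determine. That is small beside an inferred 10-point margin, but the planned sensitivity analyses could not detect it. No stated sample-size figure changes.

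**What to change.** In Statistical methods, add calendar time of entry (year, or a smooth term) to the covariates of both the propensity model and the outcome model. Define entry by the date of pre-treatment written consent, which applies to both groups alike. The matching and the weighting then inherit the term.

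Optionally, add a sentence to Sample size and recruitment saying that 218 per group is a planning target and that both groups stay open to eligible patients until overall enrolment ends. This agrees with grouping at the end of the study and removes the ambiguity about closure.

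The cost is one extra model term, plus a check that the consent date is a database field; the supplementary variable list is not shown, but consent forms are in any case sent to the study secretary. The change is best made before outcome data accumulate, since a term added later could look post hoc.
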